#### Reporting the Survey Results

To ensure a thorough description of the Delphi process, survey results will be reported following the Checklist for Reporting Results of Internet E-Surveys [142].

### Objective 2: To Identify Critical Decision Points in the Care of People With DCM—Process Mapping the Patient Journey

#### Overview

Critical decision points in the trajectory of patients will be identified using process mapping, a technique that can aptly describe the workflow and cognitive procedures associated with an activity at the desired level of granularity [143]. We define a critical decision point as a distinct juncture in the care pathway when a professional-patient discussion leads to a care decision. These are essential “go-or-no-go” decisions [59]. Our process map protocol follows the quality criteria framework set out by Antonacci et al [69] to ensure compliance with best practice recommendations. Our approach to each phase is described in the following sections.

#### Preparation, Planning, and Process Identification

The process map exercise described in this protocol is guided by the need to characterize common critical decision points that adequately represent the global DCM health care pathway. To obtain broad insights, we define the starting point as the time when a person with DCM is diagnosed with DCM and the end point as the time when a person with DCM engages in posttreatment management of the condition. We will define the patient group under investigation as people with moderate or severe DCM treated surgically and people with mild DCM treated nonoperatively [2]. This approach will ensure an all-encompassing investigation of the care route for people with DCM.

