Therefore, the application of SDM in DCM is likely highly pertinent. People with DCM encounter care decisions that are contingent upon personal, contextual, and technical factors on a fairly recurrent basis [13,37,38]. For example, the clinical manifestation of DCM has a diverse spectrum, with symptomatology that varies from person to person [39]. In the views of people with DCM, seemingly unrelated ailments such as loss of bowel or bladder control can be traced back to the spinal cord [2]. This is important as efficient monitoring of neurological deterioration and understanding when to report novel or developing symptoms is critical [40]. The decision to undergo surgery is a significant consideration, as evidenced by the frequent queries of people with DCM about the suitability of surgery and the best type of surgery for their circumstances [13,37]. For those treated surgically, a range of surgical approaches can address the degenerative changes in the cervical spine [41]. Nonetheless, the decision to offer surgery and its timing is nuanced owing to its risks and the potential for DCM to remain mild [42]. Furthermore, surgery seldom leads to a full recovery; instead, a heterogeneous and lifelong disability is generally expected [8,10-13]. The implications of this can involve multiple distinct complex care pathways, necessitating collaboration across an array of health care disciplines less familiar with DCM [43]. Therefore, it is essential that people with DCM are well prepared to navigate a host of complex decisions. Finally, although treatment decisions are often the focus of SDM tools [44], they represent one of many care decisions that patients encounter [45]. Our experience at Myelopathy.org, a DCM scientific and clinical charity, is that patient health care inquiries encompass a broad spectrum, ranging from “should I modify my day-to-day activities?” to “should I undergo a dynamic MRI?” This variability underscores the diverse range of decisions that people with DCM confront, necessitating decisional support. It is also our experience that these inquiries are often hindered by patients’ inadequate knowledge and perhaps misconceptions of DCM [45]. In this regard, people with DCM are poorly supported by a lack of comprehensive, patient-centric, and up-to-date educational resources [45].

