The aforementioned considerations, coupled with the inherent recurrent nature of decision-making in DCM, underscore the pressing need for people with DCM to engage in meaningful dialogue with health care professionals (HCPs) and have access to high-quality decisional support. In line with other chronic illness research, we hypothesize that a structured and well-orchestrated communication framework, as formulated within SDM tools, is ideally placed to successfully guide people with DCM through their health journey. Thus, investigating this area is warranted. In addition, the strategic incorporation of SDM has the potential to aptly support knowledge translation endeavors by identifying critical knowledge gaps and providing a framework for the assimilation of new knowledge into clinical practice [45-47]. This is currently a major challenge in DCM, where awareness of the condition continues to be suboptimal in the medical profession [48]. This is even conspicuous among spinal surgeons, who are considered authorities in the field of DCM [49,50]. To illustrate, a retrospective analysis of surgical decision-making in the United Kingdom found that only the amount of cord compression (as opposed to the guideline recommendations of disease severity) predicted the likelihood of a patient being offered surgery [49,51-53]. As the patient is perhaps the most motivated stakeholder and, importantly, a more recent student of DCM, addressing SDM may also support more consistent and immediate evidence-based care [54-57].

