#### Expert Selection

The sample composition significantly determines the validity of the study results [103,104]; therefore, an element of careful judgment is warranted to ensure a “balanced” panel [104-106]. To ensure a judicious selection of experts, this study will use a purposive sampling approach, drawing surgeons, other HCPs, and people with DCM as participants from the specialized RECODE-DCM community. People with DCM will be considered if they (1) have been formally diagnosed with DCM and are at least 6 months after surgical decompressive treatment, the time point at which neurological recovery is considered to halt for most [107], or (2) have undergone at least 6 months of nonoperative management [49]. Professional stakeholders will be invited to participate if they (1) are experienced in managing DCM for at least 5 years; (2) belong to key clinical disciplines, including spinal surgery, neurology, combined physical and psychological rehabilitation medicine, physiotherapy, pain management, and primary care [4,108]; and (3) have no conflict of interest in developing a CIS. All participants will be English-speaking adults (aged ≥18 years).

A diverse and geographically representative panel will be sought, in keeping with the aim of developing an internationally suitable CIS. Adequate patient involvement is vital to this endeavor to help foster evidence-based decision-making [109]. Recognizing the importance of patient perspectives, we propose aiming for a stakeholder target ratio of 1:1:2 (surgeons:other HCPs:people with DCM). The increased representation of people with DCM addresses their typically minor role in such studies and considers recent findings indicating a divergence in clinician- and patient-prioritized outcomes [4] and information needs [45]. This ratio also aligns with the status of people with DCM as the principal beneficiaries of the CIS and enhances its applicability from a patient and public perspective.

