#### Recruitment Strategy and Skills Training

Key informants—English-speaking adults (aged ≥18 years)—will be drawn from the specialized RECODE-DCM community using a convenience sampling approach. Professionals will be approached for participation if they belong to key clinical disciplines, including spinal surgery, neurology, combined physical and psychological rehabilitation medicine, physiotherapy, pain management, and primary care [4,108], and have at least 5 years of experience in managing DCM. People with DCM will be eligible if they have undergone surgical decompressive treatment at least 6 months before, the time point at which neurological recovery is considered to halt [107], and if they have experienced the common care pathway for spinal disorders from primary care to rehabilitative services [145]. This criterion will ensure that participants with DCM are familiar with a wide range of interventions and services along the global spinal care pathway and, therefore, can provide an informed view of its workflow and cognitive decision points. To ensure a global representation of the spinal care workflows and cognitive decisions, both professionals and participants with DCM will be sought at the previously described geographical target ratio. In addition, a 1:1 ratio corresponding to HCPs to people with DCM will be sought in the development of the baseline process map.

An electronic study pack will be provided to those interested in participating, comprising a written study summary, this study protocol, and a Participant Information Sheet containing the study investigators’ contact details. To equip respondents with the necessary process map skills, all consenting participants will be issued a short explanatory document outlining relevant process map symbols alongside an example of a finalized map from a different health care process. Participants will be given the opportunity to contact the study team should they have any questions or require further clarification before commencing study activities.

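### The process-map patient group names two of four severity-by-treatment combinations, is called all-encompassing, and does not match the interview eligibility rule

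*Protocol article*

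**What the plan says.** Under Objective 2, in Preparation, Planning, and Process Identification, the protocol article says the map should characterize "common critical decision points that adequately represent the global DCM health care pathway". It sets the patient group under investigation as "people with moderate or severe DCM treated surgically and people with mild DCM treated nonoperatively", and continues: "This approach will ensure an all-encompassing investigation of the care route for people with DCM".

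The Overview of Objective 2 states what is to be mapped: "We define a critical decision point as a distinct juncture in the care pathway when a professional-patient discussion leads to a care decision".

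Entry to the interviews is set separately, in Recruitment Strategy and Skills Training: "People with DCM will be eligible if they have undergone surgical decompressive treatment at least 6 months before". Patients must also have been through the usual spinal care pathway from primary care to rehabilitation. No severity condition is stated, and there is no nonoperative route in.

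The Data Analysis section of Objective 2 lists what is recorded for people with DCM: age, gender, occupation, year of diagnosis and, where applicable, treatment. Severity is not listed.

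On how treatment is decided in practice, A Role for SDM in DCM says that "the decision to offer surgery and its timing is nuanced owing to its risks and the potential for DCM to remain mild". It also cites a retrospective UK analysis in which "only the amount of cord compression (as opposed to the guideline recommendations of disease severity) predicted the likelihood of a patient being offered surgery".

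**The concern.** The definition ties treatment to severity: one treatment for each severity band. Patients whose management departed from that pairing are not in the stated group, yet the next sentence claims complete coverage of the care route. The article's own background gives reason to expect such patients, since it describes the surgical decision as a matter of judgement and reports an analysis in which severity did not predict who was offered surgery.

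This matters because the map is meant to locate decisions that shared decision-making tools could support, and Future Steps makes the maps the basis for those tools. A reader who relies on the coverage claim would assume that the routes of mild patients who had surgery, and of moderate or severe patients who did not, had been studied by design. As written, they are not part of the stated scope, and the recorded data would not show whether they had been reached.

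**Working it through.** The article gives no figure to reproduce here, and no sample-size or error-rate calculation applies. The check is to cross severity (mild; moderate or severe) with treatment (surgical; nonoperative), which gives 2 × 2 = 4 combinations, and to read each against the two rules.

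| Combination | In the defined patient group (Preparation, Planning, and Process Identification) | Eligible for patient interview (Recruitment Strategy and Skills Training) |
|---|---|---|
| Moderate or severe, surgical | Yes | Yes |
| Mild, surgical | No | Yes |
| Mild, nonoperative | Yes | No |
| Moderate or severe, nonoperative | No | No |

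1. The definition covers 2 of 4 combinations and omits 4 − 2 = 2. No other section adds the omitted two.
2. The two rules agree on only two rows: moderate or severe surgical patients are in both, and moderate or severe nonoperative patients are in neither. Only the first row can supply patient informants who also belong to the defined group.
3. Mild surgical patients may be interviewed, but their route lies outside the group that the map is said to describe.
4. Moderate or severe patients who remain unoperated can enter the map only indirectly, through clinicians' accounts.
5. Admitting nonoperative interviewees while keeping the present definition would bring in the mild nonoperative row and leave the last row out. The scope definition and the eligibility rule therefore each need attention.
6. Treatment is recorded and severity is not. From the listed variables, nobody could fill in this table for the people actually interviewed, so the coverage claim cannot be verified afterwards.

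The Delphi part of the same protocol shows that a wider rule is workable. In Expert Selection, people with DCM may enter if they "have undergone at least 6 months of nonoperative management", with no severity condition.

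**The case against.** The strongest reply is that the definition screens nobody out. It describes a group under investigation; entry is decided by the eligibility rule, which ignores severity, so one of the two omitted combinations can be interviewed anyway. The other is shut out by the surgery requirement, whatever the scope statement says. This stands in part: rewording the definition alone would not change who is interviewed, which is why both sections must change together. It does not rescue the coverage claim.

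A second reply is that other routes are open. Data Gathering asks clinicians an open question about how they manage DCM, acknowledges that pathways vary between patients, regions and guidelines, and continues to saturation. Map Generation expects variation and allows several maps. This also stands as mitigation, but such coverage would be incidental and not part of the stated scope.

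A third reply is that the aim is common decision points, so anchoring on two pathways is a legitimate choice. It would be, if stated as such. The article instead claims the whole care route, and nothing in it shows that the omitted combinations are uncommon.

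A reader might also infer more than the documents support:

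- **That the surgery decision is mapped as if severity settled it.** The map starts at diagnosis, includes operated and nonoperated groups, and targets discussions that lead to decisions. Both exits of that decision are in scope, and no section makes severity the decision rule.
- **That the omitted groups are where the choice is most open.** The article calls the decision nuanced but does not rank groups.
- **That patients who deferred surgery are all excluded.** A patient who waited and was later operated on with moderate or severe disease can satisfy both rules. The definition gives no time point for severity.
- **That the omitted share must be substantial.** The UK analysis concerns offers of surgery, not treatment received, and supplies no proportion.

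**Conclusion.** The point holds as a mismatch between the stated scope and the coverage claimed for it. Two of four severity-by-treatment combinations are outside the definition; one of those two is also outside the eligibility rule; and severity is not among the listed data that would let coverage be checked. The map remains usable, but its reach is overstated and its two population rules do not agree.

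The conclusion rests on reading the definition literally and on taking the listed participant data as what will be collected. The number of patients in the omitted groups is not given, so no size can be put on the effect beyond the count of combinations. Nothing here bears on which treatment suits which severity.

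**What to change.** Four linked edits under Objective 2:

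1. In Preparation, Planning, and Process Identification, define the patient group as people with DCM of any severity, managed operatively or nonoperatively.
2. In Recruitment Strategy and Skills Training, reconcile patient eligibility with that definition. Changing the first section alone would leave the interviewees as they are.
3. In Data Analysis, add DCM severity to the recorded patient data, beside treatment, and state the time point to which it refers.
4. Claim all-encompassing coverage only if all four combinations are represented among those interviewed. Otherwise state which pathways the map covers.

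The cost is a wording change in two sections, one extra recorded variable, and recruitment of some nonoperative informants. The map may need an additional branch, which Map Generation already allows for. The edits concern whom the map describes, not how anyone should be treated.

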#### Steering Group

It is good practice for process map exercises to be led by a steering group comprising at least one member with lived experience of the condition under investigation and a member with previous process map experience [144]. Following these recommendations, our process map activities will be supervised by the same multidisciplinary study committee overseeing the Delphi consensus process. At a minimum, the committee is envisaged to meet at the beginning and end of project activities, with further meetings as required. Decisions made at meetings will be binding when the meetings are quorate, that is, attended by at least one member of the core research team, one patient representative, and one member with process map experience. Project-relevant communications may also take place via email correspondence as necessary.

#### Recruitment Strategy and Skills Training

Key informants—English-speaking adults (aged ≥18 years)—will be drawn from the specialized RECODE-DCM community using a convenience sampling approach. Professionals will be approached for participation if they belong to key clinical disciplines, including spinal surgery, neurology, combined physical and psychological rehabilitation medicine, physiotherapy, pain management, and primary care [4,108], and have at least 5 years of experience in managing DCM. People with DCM will be eligible if they have undergone surgical decompressive treatment at least 6 months before, the time point at which neurological recovery is considered to halt [107], and if they have experienced the common care pathway for spinal disorders from primary care to rehabilitative services [145]. This criterion will ensure that participants with DCM are familiar with a wide range of interventions and services along the global spinal care pathway and, therefore, can provide an informed view of its workflow and cognitive decision points. To ensure a global representation of the spinal care workflows and cognitive decisions, both professionals and participants with DCM will be sought at the previously described geographical target ratio. In addition, a 1:1 ratio corresponding to HCPs to people with DCM will be sought in the development of the baseline process map.

An electronic study pack will be provided to those interested in participating, comprising a written study summary, this study protocol, and a Participant Information Sheet containing the study investigators’ contact details. To equip respondents with the necessary process map skills, all consenting participants will be issued a short explanatory document outlining relevant process map symbols alongside an example of a finalized map from a different health care process. Participants will be given the opportunity to contact the study team should they have any questions or require further clarification before commencing study activities.

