#### Data Gathering

To enhance accessibility and foster participant engagement [146], data will be collected using one-to-one semistructured interviews, estimated at approximately 60 minutes and conducted via Google Meet. The interview schedules will be grounded in the literature, aiming to capture information on each step of routine clinical care under investigation [144,145]. To enhance comprehensiveness and incorporate expert input, the topic guide will undergo review and approval by the aforementioned steering group. In total, 2 distinct interview guides will be developed to interview clinicians and people with DCM. For clinicians, we propose a tailored approach in recognition of the specialization inherent in each HCP’s role. For example, primary care physicians are instrumental in recognizing the condition and its associated clinical examinations for referral to a spinal surgeon [42]. Specialist surgeons, under the remit of neurosurgery or orthopedics, play a pivotal role in steering the course of management [147]. Specialist practitioners such as physiotherapists play a vital role in assisting in the management of DCM via preoperative physiotherapy and neurorehabilitation programs, primarily used in the context of DCM to manage disability postoperatively [40,148]. Therefore, our interview guide will account for differences in specialists’ knowledge of care for DCM by asking HCPs an open question regarding how they manage people with DCM in their role specifically. From there, prompts relevant to each clinician’s profession and based on the information they provide will be used to guide the interview. By grounding the topic schedule in the particularities of each professional’s role, our approach can help ensure a thorough exploration of clinicians’ perspectives, accounting for the nuanced differences across specialties and individual clinical roles within the DCM care pathway. We also recognize that the care pathways of people with DCM differ owing to variations in patients’ DCM, flow times between different regions in the world, and guidelines of care [149]. Therefore, patients will be encouraged to share their experiences navigating the care system, focusing particularly on key decision-making points. Prompts will be used to elicit detailed accounts of their journey, the information sources they relied on, their understanding of their condition at each stage, and their level of satisfaction with the decision-making process. Interviews will be conducted until data saturation is reached, that is, until no new information is identified with respect to the research question [150]. At a minimum, it is envisaged that this will involve 20 interviews with HCPs and people with DCM. To allow for the incorporation of new insights generated during the data collection process, the interview guide may be adapted as necessary [151].

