
A baseline map will be developed by interviewing 3 surgeons and 3 people with DCM from each of the geographical target areas. This approach seeks to ensure that international perspectives are adequately represented from the onset. As surgical intervention is the cornerstone treatment for DCM and surgeons preponderate the research community [50], professional transcripts derived from surgeons specifically (rather than other HCPs) will inform the preliminary map. As women remain underrepresented in clinical surgical practice [152], we will seek to recruit the views of at least one female spinal or orthopedic surgeon in the development of the baseline map. This preliminary map will be developed iteratively through a series of additional interviews with surgeons, other HCPs, and people with DCM while ensuring geographical representation. Interviews will be audio recorded and written informed consent will be sought from all participants. Following their interview, each participant will be provided with a copy of their transcript, a process map created from their interview data, and the evolving baseline map. Participants will be asked to reflect on their interviews and consider whether they wish to supplement the process map. This approach will be used as a means of ensuring data validation and quality and promoting further unbiased contributions to the data [153,154].

Upon reaching data saturation, a selection of interviews will be chosen based on their richness, and the final process maps will be refined by referring to them. Data richness will be defined as “thick” data that best capture the multifaceted complexities of the process under investigation [155]. Participants will be assigned unique study numbers to anonymize their identities in the transcripts.

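### The process map is meant to cover nonoperatively treated people with mild DCM, but the interview eligibility rule admits only patients who have had decompressive surgery

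*Protocol article*

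**What the plan says.** Under Objective 2, the section Preparation, Planning, and Process Identification sets the scope of the map: "We will define the patient group under investigation as people with moderate or severe DCM treated surgically and people with mild DCM treated nonoperatively". The map runs from diagnosis to management after treatment, and the section concludes: "This approach will ensure an all-encompassing investigation of the care route for people with DCM".

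The section Recruitment Strategy and Skills Training states who may be interviewed: "People with DCM will be eligible if they have undergone surgical decompressive treatment at least 6 months before", "and if they have experienced the common care pathway for spinal disorders from primary care to rehabilitative services". The reason given is that such people will know a broad span of services and can describe the pathway in an informed way.

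On numbers, Data Gathering states "A baseline map will be developed by interviewing 3 surgeons and 3 people with DCM from each of the geographical target areas". The baseline map is then developed further through additional interviews with surgeons, other professionals and people with DCM, continuing to saturation: "At a minimum, it is envisaged that this will involve 20 interviews with HCPs and people with DCM".

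For comparison, the Delphi panel (Objective 1, Expert Selection) uses the same 6-month postsurgical criterion but offers an alternative route for people who "have undergone at least 6 months of nonoperative management".

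**The concern.** Objective 2 exists to find the decision points in DCM care. One of the most important is whether and when to operate, and the Introduction describes that decision as finely balanced, partly because DCM may stay mild. If every patient interviewed had surgery, the patient view of that decision comes only from those for whom it went one way. This is selection on the outcome of the very decision being mapped. People who declined surgery, were not offered it, or are being followed without it are not heard.

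The later steps would not expose the gap. Saturation is judged within the eligible sample, so it can be declared without hearing any never-operated patient. Transcripts and maps go back to the interviewed participants for comment, and the final maps go to participating stakeholders, so validation draws on the same restricted set of patients. The Strengths and Limitations section does not mention the restriction. Its remark about reaching people before surgery concerns the web survey, not the interviews.

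The map is intended to inform later patient-facing decision tools, so a branch without patient testimony could carry through into those tools.

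**Working it through.** The plan gives no statistical figure to reproduce here. The check compares the sections and adds a simple count.

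**1. Target group against eligible group.**

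| | Treated surgically | Treated only nonoperatively |
|---|---|---|
| In the stated scope of the map | yes (moderate or severe DCM) | yes (mild DCM) |
| Eligible for interview as a patient | yes, if at least 6 months after surgery and with experience of care through rehabilitation | no |
| Eligible for the Delphi panel | yes, if at least 6 months after surgery | yes, after at least 6 months of nonoperative management |

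The two interview conditions are joined by *and*, so both must be met. A person who has never been operated on fails the first, whatever their experience of the pathway.

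**2. Is there another route into the interviews?** I looked through all the sections under Objective 2.

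- Data Gathering calls for further interviews with people with DCM but does not alter eligibility.
- Data Analysis lists treatment, where it applies, among the demographic items. This fits poorly with a rule under which every patient has had surgery, but it is a descriptive field and admits nobody.
- Steering Group gives supervision to the study committee, which includes 3 people with DCM (The Questionnaire, Objective 1). Their treatment is not stated, and they are not designated as interviewees.

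No other route exists.

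**3. Count.** Inputs: 3 geographical areas (Expert Selection, Objective 1), 3 surgeons and 3 people with DCM per area, and a minimum of 20 interviews in total (Data Gathering).

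- Per-area reading: 3 × 3 = 9 surgeons and 3 × 3 = 9 patients, so 9 + 9 = 18 baseline interviews. That leaves 20 − 18 = 2 to reach the minimum.
- If the 3 and 3 are read as totals across the areas: 3 + 3 = 6 baseline interviews, leaving 20 − 6 = 14.
- Never-operated patients among them: 0 of 9 on the first reading, 0 of 3 on the second, and 0 of any later patient interviews, because the same rule applies.

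The conclusion does not depend on which reading is right. The professional input to the baseline map comes from surgeons only, so at that stage both the professional and the patient accounts come from the surgical side.

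**The case against.** Several points on the other side have force.

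*Operated patients are not silent on nonoperative care.* The map starts at diagnosis, and interview prompts ask for the whole journey. A patient who later had surgery can describe an earlier nonoperative period and how the decision to operate was reached. A reader might infer that the nonoperative pathway has no patient input at all; the documents do not support that. What is missing is narrower: people never operated on, and their continuing management.

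*The nonoperative branch does not rest on clinicians alone.* A reader might infer this too, but the interview guides are grounded in the literature and approved by a steering group that includes patients, and a patient representative is needed for quorum. Pathway documents supplied by participants may also feed the map. None of this replaces an interview with someone living on that branch, but it is input.

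*The restriction has a stated reason.* Key informants chosen by convenience need not mirror the mapped population, and familiarity with many services is a sensible criterion. That justifies including operated patients. It does not explain excluding a group that the protocol says is under investigation, nor does it support the coverage claim.

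*The Delphi and the interviews set different tasks*, so different eligibility is not in itself an error. This stands. The Delphi rule matters here only because it shows that suitable wording exists and that the study already plans to recruit such people from the same community.

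*The process map is the secondary outcome* and involves no hypothesis test or effect estimate. This also stands and limits the consequences.

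**Conclusion.** The point holds as an inconsistency between the stated scope of the process map and its interview eligibility. One of the two defined patient groups can contribute 0 patient interviews. Patient accounts of the surgery decision come only from people who had surgery, and ongoing nonoperative management is without first-hand patient testimony apart from any preoperative period recalled by operated patients. The claim of complete coverage is therefore not supported for this outcome.

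The conclusion assumes that the eligibility sentence is applied as written and that no unreported exception exists. It does not depend on how the baseline interview numbers are read. It does not extend to the core information set, whose Delphi panel admits nonoperatively managed people. Nor does it show that the map will be wrong; it shows that the planned saturation and validation steps could not reveal an omission on this branch. This is a stated rule that conflicts with the stated scope, not detail left to a fuller document.

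**What to change.** Reconcile the two sections in one of two ways.

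**Option A: widen eligibility.** In Recruitment Strategy and Skills Training, add the alternative already used in Expert Selection (at least 6 months of nonoperative management). Apply the rehabilitation-pathway condition only where it is relevant to the person's care. Include nonoperatively managed people in the additional iterative interviews described in Data Gathering, and judge saturation with them included.

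**Option B: narrow the scope.** Limit the patient group in Preparation, Planning, and Process Identification, the coverage claim and the conclusions to the surgical pathway, and state the restriction among the limitations.

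**Cost.** Option A needs a change of eligibility wording, an ethics notification and possibly a few extra interviews. It should not be assumed that existing slots can simply be reassigned. The Results section reports an initial baseline map developed by the end of June 2023 (although Table 1 still lists data gathering as in planning), and on the per-area reading only 2 of the minimum 20 interviews lie beyond the baseline set. Because 20 is a minimum and interviewing continues to saturation, the design already allows the extra interviews. Option B costs only wording.
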